### Process evaluation

The concurrent mixed-methods process evaluation will aim to identify and explain the mechanisms and processes that enabled or acted as a barrier to the implementation of the cardiac rehabilitation intervention.^32 33^ The process evaluation will help build a picture of how the intervention was carried out in reality and what factors shaped it. By conducting a process evaluation, it will be possible to identify if observed impacts are solely due to the cardiac rehabilitation programme, or if these impacts are a result of external and internal variables closely linked to the environment and the context in which the intervention takes place. More specifically, the process evaluation will examine the recruitment of sites and rehabilitation teams, recruitment and reach in participants (from the recruitment log), intervention delivery to individuals (coverage, intensity), participation, retention, response of individuals to the rehabilitation intervention (data collected by the ‘Activate Your Heart’ website), unintended consequences (adverse events and inequities), contextual factors and sustained motivation for behaviour change. The website will be examined for the degree of completion of the programme, the number of occasions that the website was accessed and the extent of the change in behaviour(s) recorded. There will be a particular focus on underserved groups (women, ethnic minorities, low socioeconomic status, other PROGRESS-Plus^24^ characteristics and those without internet access or device).

Semistructured telephone or video interviews of participants (n=30) with purposive sampling to ensure diversity based on age, gender, functional impairment, treatment group, site, ethnicity and mode of delivery. A topic guide will be developed with the assistance of our Public Advisory Group and will ask about the acceptability of the rehabilitation programme and the barriers and facilitators of uptake and completion, such as family support, health inequities, lack of facilities, lack of transport, etc. However, topic guides will be iterative and informed by earlier interviews and adapted accordingly. There will be a particular focus on the acceptability and barriers to implementation in underserved groups (women, ethnic minority and low socioeconomic status). Interviews will take place at the end of the 12-week cardiac rehabilitation programme among those receiving the intervention, and between months 11 and 12 in both groups. We will interview a minimum of 10 cardiac rehabilitation staff at different time points, to gain insight into the early, medium-term and longer-term delivery of the cardiac rehabilitation programme. All of the interviews will be audio recorded and fully transcribed. Participant contact with the online discussion forum, and the ‘ask the expert’ email facility will also be examined. We will also examine data collected routinely by the website for the purposes of the national audit for cardiac rehabilitation. Qualitative data will be analysed using a thematic analysis approach.^34^ Quantitative data (recruitment logs, use of the website, recorded change in behaviours, national audit data) will be analysed using descriptive statistics to allow for the exploration of frequency of responses. All data sets will be synthesised in order to describe the complex nature of the enhanced rehabilitation intervention.

### Patient and public involvement

There has been patient and public involvement (PPI) at all stages including developing the research question, choosing outcomes relevant to patients, commenting on the burden of the intervention and of trial participation. Two PPI coinvestigators are active members of the trial management group and help to convene a public advisory group which meets throughout the trial to advise on trial procedures, especially patient-facing materials, promotional videos in multiple languages and the dissemination plan. Members of the PPI group recorded voice-overs for the promotional video in different languages.

### Ethics and dissemination

NHS research ethics approval was obtained from North of Scotland Research Ethics Committee, reference 21/NS/0116. The current protocol is version 5 (4 May 2023). Participants will provide written informed consent. A trial steering committee is providing overall supervision, and an independent data safety and monitoring committee is responsible for reviewing and assessing recruitment, interim monitoring of safety and effectiveness, trial conduct and external data.

All safety events will be recorded by researchers when they are made aware of the event by the participant, treating clinician or therapist. Adverse event reports and serious adverse events (SAEs) not related to the intervention will be entered on to the remote data entry system. Each SAE will be assessed by the relevant PI to determine whether it is related to the intervention. A related SAE will be assessed by the CI to determine whether it is expected. If the SAE is related and unexpected it will be reported to the research ethics committee and sponsor in an expedited manner.

Reporting of the trial will be consistent with the Consolidated Standards for Reporting Trials (CONSORT) 2010 Statement (patient-reported outcomes and non-pharmacological interventions).^35^ We will submit the final report to a peer-reviewed academic journal, according to our publication strategy and authorship policy. Research data will be available for secondary analysis on reasonable request.

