**Methods and analysis:**

ACTIVATE is a multicentre, parallel-group, two-arm, superiority, pragmatic randomised controlled trial, with recruitment from primary and secondary care centres in England and Wales and a target sample size of 518 (1:1 allocation; allocation sequence by minimisation programme with built-in random element). The study uses secure web-based allocation concealment. The two treatments will be optimal usual care (control) and optimal usual care plus the ‘Activate Your Heart’ web-based cardiac rehabilitation programme (intervention). Outcome assessment and statistical analysis will be performed blinded; participants will be unblinded. Outcomes will be measured at baseline and at 6 and 12 months’ follow-up. Primary outcome will be the UK version of Seattle Angina Questionnaire (SAQ-UK), physical limitations domain at 12 months’ follow-up. Secondary outcomes will be the remaining two domains of SAQ-UK, dyspnoea, anxiety and depression, health utility, self-efficacy, physical activity and the incremental shuttle walk test. All safety events will be recorded, and serious adverse events assessed to determine whether they are related to the intervention and expected. Concurrent economic evaluation will be cost–utility analysis from health service perspective. An embedded process evaluation will determine the mechanisms and processes that explain the implementation and impacts of the cardiac rehabilitation programme.

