A systematic review of exercise-based cardiac rehabilitation for adults with stable angina,^9^ identified seven randomised controlled trials (RCTs) (n=581) with high risk of bias. It found low-quality evidence that cardiac rehabilitation resulted in a small improvement in exercise capacity compared with usual care with standard mean difference 0.45 (95% CI 0.2 to 0.7), and uncertainty about the effect on all-cause mortality, acute MI, cardiovascular-related hospital admissions, quality of life and cardiac rehabilitation-related adverse events. These RCTs were small in size and recruited mainly white middle-aged men. More evidence is needed from under-represented groups including women, older age groups, ethnic minorities and those with comorbid conditions. Web-based programmes might increase the reach of cardiac rehabilitation, and there has been one small RCT (n=94) of such a programme (‘Activate Your Heart’), which demonstrated that it was possible to provide cardiac rehabilitation to people with chronic stable angina.^10^ Trial methods were feasible in terms of recruitment, retention and outcome measurement. After 6 months, there were statistically significant lower levels of angina frequency, but a larger RCT is needed to test longer-term effectiveness and cost-effectiveness.

‘Activate Your Heart’ has the potential to improve physical and mental health with minimal risk. There may be a risk of injury or provoking an episode of angina when exercising, however, the physical activity goals are carefully graded and the programme has an excellent safety record.^10^

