### Trial treatment/interventions

We plan to compare web-based cardiac rehabilitation in addition to optimal usual care (intervention) with optimal usual care alone.

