General Self-Efficacy scale^18^	Measures optimistic self-belief to cope with a variety of difficult demands in life. Higher score indicates greater self-efficacy.	(10–40)
International Physical Activity Questionnaire^20^	This questionnaire supplements the accelerometer data by providing self-reported duration (minutes) and frequency (days) of physical activity in the previous 7 days in the domains: job related, transportation, housework, recreation and sitting.	Minutes of light, moderate and vigorous physical activity
Patient Completed Economic Measures		
EQ-5D-5L^22^	Health utility index with five dimensions (mobility, self-care, usual activities, pain/discomfort, anxiety/depression) and five levels to give health states converted to a utility weight. Also Visual Analogue Score (VAS) for health state today	Health utility weight from 0 (death) to 1.0 (perfect health) also with negative values VAS (0–100)
Client Service Receipt Inventory^23^	Collects information about health service use, including medication, smoking cessation, diet management, weight control programmes and exercise referral schemes.	According to activity
Objective measures of physical activity and function		
Physical activity measured with the ActivPAL accelerometer^19^	The ActivPAL device is a small, slim monitor worn on the thigh. It provides accelerometer-derived information about thigh position and acceleration to determine body posture (sitting, lying or upright), stepping and stepping speed (cadence), from which energy expenditure can be inferred. It will be worn for 7 days to measure step count, energy expenditure, duration of sedentary, light, moderate and vigorous physical activity. Participants will be asked to keep a wear diary documenting working hours, sleep, removal reasons and any other comments.	Step count, energy expenditure, duration of sedentary, light, moderate and vigorous physical activity
Incremental Shuttle Walk Test^21^	Progressive walking test that requires the participant to walk up and down a 10 m course, at a speed dictated by an audio signal. The time between signals is reduced every minute and there are 12 levels. The test ends when the participant either (a) is too breathless to maintain the required speed or (b) fails to complete a shuttle in the time allowed or (c) reaches 85% of the predicted maximal heart rate.	Metres walked

EQ-5D-5L, EuroQol-5 Dimensions-5 Levels; MRC, Medical Research Council.

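### As the article words it, an unexpected serious adverse event caused by the shuttle walk test would be handled as not related to the intervention and would get no expedited report

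*Protocol article*

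**What the plan says.** The protocol article sets out the SAE route in Ethics and dissemination. It begins with one causality question: "Each SAE will be assessed by the relevant PI to determine whether it is related to the intervention". Events that fail it are dealt with in the sentence before: "Adverse event reports and serious adverse events (SAEs) not related to the intervention will be entered on to the remote data entry system". Events that pass it go on: "A related SAE will be assessed by the CI to determine whether it is expected". The last step is: "If the SAE is related and unexpected it will be reported to the research ethics committee and sponsor in an expedited manner". The abstract (Methods and analysis) gives the same criterion: "serious adverse events assessed to determine whether they are related to the intervention and expected".

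The section on trial treatment and interventions fixes what the intervention is: "We plan to compare web-based cardiac rehabilitation in addition to optimal usual care (intervention) with optimal usual care alone". The Incremental Shuttle Walk Test is listed elsewhere, among the outcome measures (Outcomes, Table 1). One of its three end points is that the participant "reaches 85% of the predicted maximal heart rate"; the others are breathlessness and a failed shuttle. Table 2 schedules the test at baseline, 26 and 52 weeks without restriction by arm. In the same table, the rows for monitoring adverse events and SAEs are first marked at 7 days after randomisation.

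**The concern.** The trial exposes participants to exertion in two ways. One is the programme, in the intervention arm only. The other is the walk test, in everyone. The causality question covers the first and is silent on the second. If a site follows the wording, a serious event brought on by the test gets the answer 'not related', and the two later steps, expectedness and expedited reporting, do not apply to it.

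What is at stake is prompt notice of harm from a research procedure, in a population selected for angina with evidence of myocardial ischaemia. Anyone who later reads the list of related SAEs as the harm of taking part in the trial would also be reading an incomplete list, because it answers a question about the programme alone.

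**Working it through.** The point is mainly a reading of the text. Arithmetic enters only to show how much testing is involved.

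**1. The sample size that sets the number of tests.** Inputs from Sample size: difference 8, SD 25, 90% power, 5% significance, 20% loss. The normal approximation, 2 × 25² × (1.960 + 1.282)² / 8², gives 206 per group after rounding up. The t-test version gives 206.19, rounded up to 207, which is the article's figure. Then 207 / 0.8 = 258.75, rounded up to 259 per group, and 259 × 2 = 518. The article's numbers reproduce.

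**2. Planned walk tests.** Table 2 gives three per participant.
- All: 518 × 3 = 1,554, of which 259 × 3 = 777 are in people allocated to control.
- Baseline: 518. Randomisation procedures places randomisation after the baseline assessments, so these tests precede allocation.
- After randomisation: 518 × 2 = 1,036 at most, of which 259 × 2 = 518 are in controls.
- If the full 20% loss applied at both follow-ups: 414 × 2 = 828 after randomisation (207 × 2 = 414 in controls), and 518 + 828 = 1,346 in total.

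**3. The route of an unexpected SAE under the stated rule.**

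| Cause and time of the SAE | Related to the programme? | Expectedness assessed? | Expedited? |
|---|---|---|---|
| Programme, intervention arm | Yes | Yes | Yes |
| Walk test at 26 or 52 weeks, intervention arm | No | No | No |
| Walk test at 26 or 52 weeks, control arm | No | No | No |
| Walk test at baseline | No, since nobody has yet received the programme | No | No |

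**4. Whether another sentence closes the gap.** No part of the article gives a test of relatedness to trial procedures or a second expedited route. Two other provisions do apply. Researchers are to record every safety event they are made aware of, and an independent committee is responsible for interim safety monitoring. These cover capture and periodic review. They do not supply the expectedness judgement or the prompt report.

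**5. The baseline visit.** Table 2 places consent at screening and the first walk test at baseline, but marks neither adverse event nor SAE monitoring in the baseline column. One third of the planned tests (518 of 1,554) therefore precede the first scheduled monitoring mark. The general commitment to record all safety events may cover them, but the table does not show it.

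**The case against.** The strongest objection is that this is a journal article. It names version 5 of the full protocol, which is not shown and may define relatedness to include trial procedures. Definitions, timelines and form content are commonly left there. This stands as a limit on how far the conclusion reaches. It does not remove the point, because the article does not merely leave the definition out: it states a criterion, twice, and builds a complete route on it.

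Four stronger readings are tempting, and the documents do not support them.

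- *That test-caused events would be lost, or could never be expedited.* All safety events are to be recorded, the 26- and 52-week visits carry SAE monitoring in both arms, and an independent committee reviews safety. With version 5 unseen, nothing stronger than 'on this wording' is justified.
- *That the control arm is wrongly treated because none of its SAEs can count as related.* No intervention-related events among people who do not receive the intervention is the right answer to that question. The article does not offer that count as reassurance about the walk test.
- *That the article admits the test is hazardous.* The sentence "There may be a risk of injury or provoking an episode of angina when exercising" is in the Introduction and concerns exercise within the programme; it goes on to cite graded goals and the programme's safety record. No harm from the test is reported, and the heart-rate limit caps exertion.
- *That a number of missed reports can be predicted.* The article gives no SAE rate for the test. Any such figure would rest on an unsourced rate and would overcount, since only unexpected events are expedited and some test-provoked events could be judged expected.

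It is also fair to say that nothing here touches the primary outcome or its analysis.

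**Conclusion.** The point holds as a defect in the stated safety rule. On the wording in Ethics and dissemination and in the abstract, an unexpected SAE caused by the shuttle walk test would be handled as not related to the intervention, in either arm. It would be recorded and open to committee review, but would get no expectedness assessment and no expedited report. Table 2 adds a smaller inconsistency, with no safety monitoring marked at the visit where the first test is done.

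Its size is best given as exposure: up to 1,554 planned tests, 518 before randomisation and up to 1,036 after. How many serious events those tests would cause cannot be derived from the document, and the conclusion does not depend on it. Trial status reports 68 of 518 participants recruited at submission, so most of the planned testing still lay ahead then.

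The conclusion assumes that 'the intervention' carries the meaning the article gives it, and that sites apply the rule as the article states it. If version 5 is wider, the fault is in the article's description and not in the conduct of the trial.

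**What to change.** In Ethics and dissemination and in the abstract, change the criterion to 'related to the intervention or to any trial procedure' and apply it to all participants. Record the two causes as separate fields on the SAE form, so that programme-related and test-related events can be shown apart in each arm. Send related and unexpected events down the existing expedited route; no new route is needed. Reconcile Table 2 with the visit schedule so that safety events are captured from the baseline walk test onward.

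Check version 5 first. If it already defines relatedness this way, correct only the article's wording.

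The cost is a change of wording in two places, a correction to Table 2, one extra form field and possibly a few more expedited reports. The assessments, the analysis and the clinical care of participants stay as they are.

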### Trial status

The first participant was recruited in July 2022. At the time of submission this trial had been open in 20 sites, with 10 more sites in preparation and had recruited 68 participants. Updated recruitment information can be found on the trial website (http://activate-trial.org.uk).
